**16. PRIOR AND CONCOMITANT MEDICATIONS, NON-DRUG THERAPIES AND PROCEDURES**

Prior medications are defined as medications taken prior to the first dose of study drug. Concomitant medications are defined as medications taken at the time of first dose or after the first dose of study drug is administered. All medications as documented by the investigator will be coded using the Anatomical Therapeutic Chemical (ATC) code making use of the World Health Organization drug dictionary (WHODD) version 01 SEP 2021 and the Preferred name (PN).

Prior and concomitant medications (other than systemic antibiotics) will be summarized separately by treatment group, ATC and PN as well as overall by ATC and PN class in the Safety analyses set. If medications are taken continuously before and after the randomization visit then that medications will be included in both prior and concomitant medication summaries.

Prior and concomitant systemic antibiotics will be summarized separately by treatment, ATC and PN as well as overall by ATC and PN in the MITT analyses set. Also, a summary of systemic antibiotics within 72 hours prior to randomization will be provided.

For the summary tables, if a subject has taken a prior or concomitant medication more than once, the subject will be counted only once for the medication.

All reported medications will be included in the listing.

Similarly, Non-drug Therapies and Concomitant procedures will be summarized by Treatment Group in the Safety analyses set. Non-drug Therapies are coded using WHO Drug dictionary version 01 SEP 2021 and Concomitant procedures are coded using the MedDRA dictionary (Version 25.1).

[figure not shown]

## 17. TREATMENT EXPOSURE

Duration of therapy will be calculated as the last dose date/time of therapy minus the first dose date/time of therapy +1. Summary tables will include descriptive statistics as well as the number and percentage of subjects in each treatment group with duration of therapy in the following categories:  $\leq 2$ ,  $2 < \text{to } 3$ ,  $3 < \text{to } 4$ ,  $4 < \text{to } 5$ ,  $5 < \text{to } 6$ ,  $6 < \text{to } 7$  and  $> 7$  days.

The compliance rate to therapy will be calculated as the total number of doses received divided by the total number of doses expected then multiplied by 100. The total number of expected doses is the number of medication days multiplied by the number of expected doses per day. Number of medication days is the total number of days from the date/time of the first dose of study drug to the date/time of the last dose of study drug. If a subject receives  $\leq 48$  hours of therapy, the expected doses will be calculated assuming the subject received full 48 hours therapy. Although receipt of  $>7$  days of therapy would be a protocol deviation, if a subject receives  $>7$  days therapy, the expected doses will be calculated assuming the subject received 7 days therapy.

Percent compliance to therapy will be calculated using the following formula:

$$\% \text{compliance} = \frac{\text{no. of doses received} * 100}{\text{expected doses per day} * \text{total number of medication days}}$$

The number and percentage of subjects with % compliance:  $<80\%$ ,  $80-120\%$  and  $> 120\%$  will be tabulated in each treatment group.

All summaries will be provided for the Safety and mMITT population.

[figure not shown]

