## **6. SUMMARY OF THE STUDY DESIGN**

This is a Phase III, prospective, multicentre, randomised, double-blind, comparative efficacy and safety study of oral nafithromycin versus oral moxifloxacin for the treatment of male and female adults with CABP. Subjects providing informed consent and meeting all study eligibility criteria will be enrolled in the study and randomised in a 1:1 ratio to either of the following 2 treatment arms:

- Nafithromycin 800 mg (two 400-mg tablets) orally (PO) every 24 hours (q24h) for 3 days; subjects will receive matching placebo PO q24h on Day 4 through EOT (2 tablets) and matching moxifloxacin placebo PO q24h, on Day 1 through EOT (1 capsule), to maintain the blind (2 tablets and 1 capsule in total).
- Moxifloxacin 400 mg (1 capsule: Over-encapsulated tablet) PO q24h for 7 days; subjects will receive matching nafithromycin placebo PO q24h on Day 1 through EOT (2 tablets), to maintain the blind (2 tablets and 1 capsule in total).

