### **12.7 CLINICALLY EVALUABLE (CE) ANALYSES SET**

[figure not shown]

The CE analyses set will include all MITT subjects who follow important components of the trial. To be included in the CE analyses set, subjects must meet all of the following criteria:

- Meet key Inclusion Criteria, including the clinical disease criteria for CABP (Inclusion Criteria #3a, #3b, #3c, #3d and #3e in the protocol)
- Do not meet key Exclusion Criteria (#1 through # 6, #16 and #18 in the protocol)
- The TOC Visit occurred within a window of 11 to 21 days. Days from the date of randomisation unless the subject was deemed a clinical failure before this visit. Note that for the purpose of this SAP, the window has been widened from 11 to 19 days to 11 to 21 days in order to allow inclusion of subjects whose visit to the clinic was delayed for social reasons
- Do not receive non-study, potentially effective against the baseline pathogen(s), systemic antibacterial therapy between Day 1 and the assessment TOC
- Do not have a clinical outcome of Indeterminate at the TOC Visit
- Receive at least 80% of the intended doses of randomised study drug therapy (based on number of tablets dispensed/received)
- Receive at least 48 h of study drug therapy to be considered an evaluable clinical failure and at least 72 h of study drug therapy to be considered an evaluable clinical success
- Do not have any other significant protocol violation(s) that may confound efficacy assessments at TOC

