| 4                             | Subject who was dosed incorrectly, had large departures from dosing schedule or was otherwise non-compliant with study drug                                                                                                                                  | Incorrect dosing or non-compliance with study drug administration |
| 5                             | Subject who was dosed more than 7 days                                                                                                                                                                                                                       | Received > 7 days of study drug                                   |
| 6                             | Subject who received a non-study systemic antibacterial agent with potential activity against CABP pathogens                                                                                                                                                 | Received prohibited systemic antimicrobial                        |
| 7                             | Subject who received another prohibited medication as defined in the protocol                                                                                                                                                                                | Received other prohibited medications (non-antimicrobial)         |
| 8                             | PDs that impact efficacy assessments and are directly related to the study endpoints such as delayed or missed or assessments done outside of the protocol-defined windows at Day 4, EOT and TOC visits, deviations on the IP management and administration. | Missed, incomplete or non-adherence to efficacy assessments       |
| 9                             | Deviations relating to informed consent document administration. (e.g. Study specific procedure performed prior to obtaining Informed Consent, Subject signed incorrect ICF version, and subject did not sign the most recent version of the ICF at          | Informed consent deviation                                        |

[figure not shown]

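### The SAP's duration and compliance formulas misstate exposure, and the 80% rule for the CE set counts tablets, which read literally are all placebo in the moxifloxacin arm

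*SAP*

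**What the plan says.** SAP Section 17 uses two day counts. For duration: "Duration of therapy will be calculated as the last dose date/time of therapy minus the first dose date/time of therapy +1". The result is tabulated in bands, the top one being more than 7 days.

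For compliance, "The total number of expected doses is the number of medication days multiplied by the number of expected doses per day". Medication days run up to the subject's last dose, and no day is added here: "Number of medication days is the total number of days from the date/time of the first dose of study drug to the date/time". A floor and a cap apply. With 48 hours of therapy or less, "the expected doses will be calculated assuming the subject received full 48 hours therapy"; above 7 days, the subject is treated as having had 7. Compliance is banded as below 80%, 80-120% and above 120%.

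On long treatment, Section 17 remarks: "Although receipt of $>7$ days of therapy would be a protocol deviation". Significant deviation 5 in Table 1 (Section 14) reads: "Subject who was dosed more than 7 days".

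The CE set (Section 12.7) has its own adherence rule: "Receive at least 80% of the intended doses of randomised study drug therapy (based on number of tablets dispensed/received". In Section 6 the moxifloxacin arm gets its active drug as one capsule a day for 7 days, and "subjects will receive matching nafithromycin placebo PO q24h on Day 1 through EOT (2 tablets" a day. In the nafithromycin arm the tablets are active on Days 1 to 3 and placebo after that, and the capsule is placebo throughout. Section 6 totals tablets and capsule separately.

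**The concern.** Adding 1 is right for calendar dates, where the first and last day both count. Added to a difference of date/times, it lets a few minutes on the clock decide whether a completer is shown as treated for longer than the planned 7 days.

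The compliance denominator ends at the subject's own last dose, so days not taken after stopping are never expected. It also omits the added day, so n gap-free daily doses are divided by n − 1 days. A compliance table built this way can show early stoppers as over-compliant.

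The CE rule counts units that, in one arm, contain no active drug. Table 2 (Section 19.3) uses the CE set for secondary comparisons at Day 4, EOT and TOC. Readers will take that set as the one that followed the regimen.

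**Working it through.** The SAP states no numerical result here to reproduce, so its formulas are applied to a once-daily, 7-dose course.

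**Inputs.** Duration, compliance, floor and cap: Section 17. Dosing every 24 h ± 4 h, with a further 4 h on Day 2: schedule footnote t, Section 8. Units per day by arm: Section 6. CE threshold: Section 12.7.

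**(a) Duration = (last − first date/time) + 1.** Seven doses exactly 24 h apart span 6 days: 6 + 1 = 7.00, in the band ending at 7. If the last dose is:
- 15 minutes later on the clock than the first: 6 + 0.25/24 + 1 = 7.01, so >7;
- 1 h later: 7.04, so >7;
- 4 h later: 6 + 4/24 + 1 = 7.17, so >7;
- 4 h earlier: 6 − 4/24 + 1 = 6.83, so not >7.

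This takes the window as anchored to the Day 1 clock time; use of the extra Day 2 allowance could widen the range. The share of completers in >7 is the share whose last dose is later on the clock than the first. The SAP does not give it: it could be anything from none to all, and is one half if timing is symmetric (assumption).

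**(b) Compliance = 100 × doses / medication days**, with a floor of 2 days and a cap of 7, for subjects who miss no dose before stopping, at exact 24 h spacing:

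| Doses taken | Literal (no added day) | With the added day | Against 7 planned |
|---|---|---|---|
| 1 | 1/2 = 50% | 1/2 = 50% | 14% |
| 2 | 2/2 = 100% | 2/2 = 100% | 29% |
| 3 | 3/2 = 150% | 3/3 = 100% | 43% |
| 4 | 4/3 = 133% | 4/4 = 100% | 57% |
| 5 | 5/4 = 125% | 5/5 = 100% | 71% |
| 6 | 6/5 = 120% | 6/6 = 100% | 86% |
| 7 | 7/6 = 117% | 7/7 = 100% | 100% |

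On the literal reading, stops after 3, 4 or 5 doses fall above 120%. Someone dosed through Day 7 with two doses missed on the way scores 5/6 = 83% literally, inside 80-120%, but 5/7 = 71% with the added day.

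**(c) CE rule.** Seven days × 2 tablets = 14 tablets; 80% of 14 = 11.2, so 12 tablets (6 days) are needed. Read literally:
- Moxifloxacin arm: 14 of 14 tablets are placebo, and the 7 active units are capsules, which are not counted.
- Nafithromycin arm: 3 × 2 = 6 of 14 tablets are active. Missing one of the three active days leaves 12/14 = 86%, a pass. Taking all three and stopping after Day 5 gives 10/14 = 71%, a fail.

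**The case against.** Several stronger statements are tempting, and the SAP does not support them.

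- *Every early stopper scores 100% or more.* No. The 48-hour floor gives a one-dose stopper 50%, and doses missed before stopping lower the score.
- *Poor adherence cannot be detected.* No. The Section 17 duration bands and the Section 13 disposition table show early stopping by arm. Significant deviation 4 covers non-compliance. The CE rule uses intended doses and so catches early stopping, as the 71% example shows. Only the compliance percentage hides it.
- *On-schedule completers will be recorded as significant deviations.* The SAP does not say that deviation 5 is derived from the duration formula. What follows is a table that appears to contradict the deviation listing.
- *The non-inferiority conclusion is at risk.* The primary test uses the MITT set, which requires one dose (Sections 12.3 and 19.1). No efficacy analysis uses the Section 17 compliance figure.

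Two milder readings also deserve weight. The 7-day cap for a 7-day course suggests that inclusive counting was meant, which would remove the 117% and 150% figures. But the text does not say so, and gap-free stops after 2 to 6 doses still score 100%. Compliance while on treatment is a legitimate measure, but the table should then be labelled that way. Similarly, Section 6 describes the capsule as an over-encapsulated tablet, so the CE wording may be meant to cover it. Since that section counts tablets and capsule separately, the CE rule should say which it means.

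**Conclusion.** The point holds for what Section 17 tabulates and for one CE criterion. Completers dosed within the window are shown at about 6.83 to 7.17 days, and those with a later last clock time fall in >7 days. That assumes fractional days are kept: the SAP states no rounding, and rounding to whole days would bring these values to 7. Compliance is wrong on the literal reading (117% for a perfect course; 150%, 133% and 125% for gap-free stops after 3, 4 and 5 doses). On the inclusive reading it is uninformative about stopping (100% for gap-free stops after 2 to 6 doses, against 29% to 86% of the planned course). The CE threshold, read literally, judges comparator adherence on placebo units.

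The consequences are limited to the exposure and compliance tables (Safety and mMITT sets) and to CE membership, which feeds secondary comparisons. How many subjects would change CE status cannot be derived from the SAP.

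**What to change.** 1. **Duration:** last dose date minus first dose date + 1, on calendar dates. Doses on Days 1 to 7 then give exactly 7.
2. **Compliance:** divide by the planned 7-day course. If an on-treatment measure is kept, use the same inclusive day count as for duration and label the table as on-treatment compliance.
3. **CE set:** count tablets and capsules, and require 80% of each, under blind and identically in both arms. Say what intended doses means for a subject who stops as a clinical failure, because the same list admits failures after 48 h while 80% of 7 days requires 6 daily doses.
4. **Active-unit adherence by arm:** report only as a descriptive summary after unblinding. As a CE criterion it would set unequal standards: one missed active dose fails in the nafithromycin arm (2/3 = 67%) and passes in the moxifloxacin arm (6/7 = 86%).

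The cost is SAP wording and programming, with no new data if the dosing records separate tablets from capsules. The downside is that somewhat fewer subjects will be shown as compliant or included in the CE set.

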## 18. STUDY EFFICACY VARIABLES / ENDPOINTS

### 18.1 Primary Efficacy Endpoints

Clinical Response at Day 4 (MITT Analyses set)

- Favourable Clinical Response: Alive and improvement of at least 1 level (e.g., severe to moderate, moderate to mild, mild to absent) in at least 2 CABP symptoms (dyspnoea, cough, production of purulent sputum or pleuritic chest pain) compared with that at the Baseline Visit, without worsening in any other of the 4 CABP symptoms. Severity of symptoms is based on a 4-point scale (absent, mild, moderate or severe).
- Unfavourable Clinical Response: No improvement of at least 1 level in at least 2 CABP symptoms compared with that at baseline; or worsening in any of the 4 CABP symptoms compared with that at baseline; or death from any cause at or before Day 4.
- Indeterminate: Study data are missing for evaluation of efficacy at Day 4 for any reason, including loss to FU.

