## Statistical Analysis Plan (SAP) for Protocol W-4873-301

[figure not shown]

vPrior medications that have been administered within 14 days before the date of signing the informed consent or during the Screening Phase will be recorded in the electronic Case Report Form (eCRF). All medications administered after the first dose of the study drug must be recorded in the eCRF.

wBest possible efforts should be made to conduct an in-person visit. In the event that an in-person visit is not possible due to any reason, assessment may be conducted through a telephone contact.

[figure not shown]**9. SAMPLE SIZE**

This study is designed to demonstrate non-inferiority of oral nafithromycin (800 mg once daily) compared with oral moxifloxacin (400 mg once daily).

Nafithromycin will be declared non-inferior to moxifloxacin if the lower limit of the 2-sided 95% confidence interval (CI) for the difference between treatment groups (nafithromycin minus moxifloxacin) in the proportion of subjects with a favourable clinical response at Day 4 in the MITT analyses set is greater than -0.125.

In these comparisons, the margin of 12.5% has been determined based on historic data regarding the treatment effect of antibiotics.

For the determination of the study sample size, favourable clinical response rates at Day 4, obtained from studies of subjects with CABP, of 85% to 90% are projected, with an anticipated dropout rate by Day 4 of at most 5%. However, since subjects who dropout from the study prior to Day 4 will be included in the denominator for the calculation of the proportion of subjects with favourable clinical response at Day 4, an attained favourable response rate at Day 4 of 81% to 86% is anticipated in each treatment group. Based on these attained favourable clinical response rates at Day 4, a non-inferiority margin of 12.5%, and using the Farrington-Manning sample size approach for the Miettinen and Nurminen method, it has been determined that approximately 414 adult subjects (207/arm) will need to be included in the MITT analyses set in order for the statistical test to have a-priori at least 90% power at the 1-sided 2.5% significance level when the attained favourable response rate is at least 81%. Given the number of subjects needed in the MITT (N=414) analyses set and assuming a TB rate of 15%, 488 subjects will need to be enrolled into the study.

[figure not shown]

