#### *Investigator determined Clinical Outcome at EOT (MITT, mMITT and CE Analyses Sets)*

- Clinical Cure: Alive and signs and symptoms of CABP (dyspnoea, production of purulent sputum or pleuritic chest pain) are resolved or return to premorbid conditions and cough is improved such that further antibacterial therapy is no needed and the subject otherwise cannot be declared a clinical failure.
- Clinical Failure: The signs and symptoms of CABP (dyspnoea, production of purulent sputum or pleuritic chest pain) did not resolve or return to premorbid and/or cough worsened, such that non-study antibacterial therapy must be initiated for the treatment of CABP or death occurred prior to assessment or subject received alternative anti-microbial therapy for the treatment of CABP prior to this visit.

[figure not shown]

- Indeterminate: Study data are missing for the evaluation of efficacy at the assessment visit for any reason, including loss to FU.

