### 19.1 Primary Efficacy Analysis

The primary efficacy endpoint for this study is the proportion of subjects with favourable clinical response at Day 4 in the MITT analyses set. Subjects will be categorised as having Favourable, Unfavourable or Indeterminate response. Subjects with missing data or who are lost to follow-up (FU) are defined as Indeterminate and will be included in the denominator for the calculation of the proportion of subjects with Favourable clinical response at Day 4.

The number and percentage of subjects in each treatment group and in each response category will be reported.

The null ( $H_0$ ) and alternative ( $H_1$ ) hypotheses are the following:

$$H_0: \pi_1 - \pi_2 \leq -0.125 \text{ vs. } H_1: \pi_1 - \pi_2 > -0.125$$

Where:

$\pi_1$  = the proportion of subjects with favourable clinical response at Day 4 in the nafithromycin treatment group

$\pi_2$  = the proportion of subjects with favourable clinical response at Day 4 in the moxifloxacin treatment group

The non-inferiority hypothesis test is a 1-sided hypothesis test performed at the 2.5% level of significance. The statistical test is based on the lower limit of the 2-sided 95% CIs for the observed difference in the proportion of subjects with favourable clinical response at Day 4 (nafithromycin minus moxifloxacin). The CI will be obtained using the method of Miettinen and Nurminen.

If the lower limit of the 2-sided 95% CI for the difference between treatment groups (nafithromycin minus moxifloxacin) in the proportion of subjects with favourable clinical response rates at Day 4 in the MITT analyses set is greater than  $-0.125$ , the null hypothesis  $H_0$  will be rejected in favour of the alternative hypothesis  $H_1$  and the non-inferiority of nafithromycin monotherapy to moxifloxacin will be concluded. In addition, if the lower limit of the 2-sided 95% CI for the difference between treatment groups (nafithromycin minus moxifloxacin) in the proportion of subjects with favourable clinical response rates at Day 4 is greater than zero, the superiority of nafithromycin monotherapy to moxifloxacin monotherapy will also be concluded.

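### The Day 4 primary response has no rule for non-study antibacterials given before the assessment, and no planned Day 4 analysis scores such rescue as a failure

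*SAP*

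**What the plan says.** **Day 4 (SAP Section 18.1).** Favourable requires survival, a one-level gain in two or more of the four symptoms, and no symptom worse. Unfavourable is "No improvement of at least 1 level in at least 2 CABP symptoms compared with that at baseline; or worsening in any" of the four symptoms, or death by Day 4. Indeterminate is missing data. Section 19.1 uses the same three classes: "Subjects will be categorised as having Favourable, Unfavourable or Indeterminate response". None of them mentions non-study antibacterial therapy.

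**EOT and TOC (Section 18.2).** Clinical Failure includes the case where the "subject received alternative anti-microbial therapy for the treatment of CABP prior to this visit". TOC uses the same definitions and carries EOT failures forward.

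**Other Day 4 analyses.** Section 19.2 plans two sensitivity analyses: one stratified by PORT class, and one that recodes Indeterminate as favourable. The CE set (Section 12.7) excludes subjects given potentially effective non-study systemic antibacterials between Day 1 and TOC. Section 23 adds no rescue rule, and Section 26 lists no change to the Day 4 definition.

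**Such therapy is foreseen.** Footnote q of the schedule (Section 8) speaks of clinical failures who need other antibacterial treatment. Table 1 (Section 14) lists non-study antibacterials as significant deviation 6. Section 16 summarises concomitant systemic antibiotics in the MITT set.

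**The concern.** A subject who does poorly on study drug, is switched on Day 2 or 3 and is better on Day 4 is credited to the randomised drug on the primary endpoint. Three days later the same subject is a failure. The SAP thus treats rescue as informative about failure at EOT and TOC but is silent on it at Day 4, where the confirmatory claim is made.

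In a non-inferiority comparison, crediting rescue matters most when the test drug is the weaker one. More of its failures would then be rescued and counted as successes, and the observed difference would move toward zero. The same Day 4 difference also carries the superiority claim in Section 19.1.

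**Working it through.** **1. Follow one subject through the definitions.** Take a MITT subject given another antibacterial for CABP on Day 2 or 3 who, on Day 4, is one level better in two symptoms with none worse.

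| Analysis | Result |
|---|---|
| Day 4, MITT, primary | Favourable |
| Day 4, stratified by PORT class | Favourable |
| Day 4, Indeterminate recoded | Favourable (the subject is not Indeterminate) |
| Day 4, CE | Removed, if the agent is potentially effective against the baseline pathogen |
| EOT and TOC, MITT | Clinical Failure |

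No Day 4 row scores the subject as a failure. A switched subject with no Day 4 assessment is Indeterminate and already counts as non-favourable in the primary analysis.

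**2. Reproduce the design figures (Section 9).** The inputs are "a non-inferiority margin of 12.5"%, "at least 90% power at the 1-sided 2.5% significance level when the attained favourable response rate is at least 81"%, and the test level: "The non-inferiority hypothesis test is a 1-sided hypothesis test performed at the 2.5% level of significance".

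- Attained rates: the projection is "favourable clinical response rates at Day 4, obtained from studies of subjects with CABP, of 85% to 90% are projected". The SAP allows for losses of 5% or less before that visit. So 0.85 × 0.95 = 0.8075 and 0.90 × 0.95 = 0.855, which match the SAP's 81% and 86%.
- n per arm by the unpooled normal formula: (1.960 + 1.282)² × 2 × 0.81 × 0.19 / 0.125² = 207, as stated. The Farrington-Manning formula with restricted null variance gives 211, within 3%.
- Power at 207 per arm is 89.4% (Farrington-Manning) or 89.8% (exact enumeration of the Miettinen-Nurminen test).
- Enrolled: 414 / 0.85 = 487.06, rounded up to 488.

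The sample size is not in dispute; these figures serve as the base for what follows.

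**3. Size of the shift.** The shift toward zero is (rescue rate on nafithromycin − rescue rate on moxifloxacin) × share of rescued subjects who meet Favourable on Day 4. The SAP gives none of these rates, so all are assumed.

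- 2% versus 1%, 60% improved: 0.6 × 1 = 0.6 points, or 0.6 / 12.5 = 5% of the margin.
- 6% versus 2%, 60% improved: 0.6 × 4 = 2.4 points, or 2.4 / 12.5 = 19% of the margin.
- Equal rates: 0 points.

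**4. Effect on the false-claim rate.** Put the truth, with rescue scored as failure, on the null boundary: 68.5% versus 81%, 207 per arm. Suppose a fraction f of the failures in each arm (31.5% and 19%) is rescued, improves by Day 4 and is counted Favourable. The expected rates become 68.5 + 31.5f and 81 + 19f. The last column is the exact Miettinen-Nurminen probability of declaring non-inferiority.

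| f | Nafithromycin | Moxifloxacin | Difference (points) | P(declare) |
|---|---|---|---|---|
| 0 | 68.5% | 81.0% | −12.5 | 2.5% |
| 5% | 70.1% | 82.0% | −11.9 | 3.5% |
| 10% | 71.7% | 82.9% | −11.25 | 4.9% |
| 20% | 74.8% | 84.8% | −10.0 | 9.3% |

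If instead 2 points are rescued and improve in each arm (70.5% versus 83%), the probability stays at 2.5%. If it is 2 points on nafithromycin and 5 on moxifloxacin (70.5% versus 86%), it falls to 0.3%.

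**5. Power if rescue were scored Unfavourable in the primary analysis.** If that lowers both arms from 81% by an assumed 1, 2 or 3 points, Farrington-Manning power at 207 per arm is 88.4%, 87.3% or 86.3%, against 89.4% with no lowering.

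**The case against.** A reader might infer that the definition as written biases the trial toward non-inferiority and that the primary endpoint must be rewritten. The SAP does not support that reading.

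- **Direction is conditional.** The bias favours non-inferiority only if rescue with improvement is more frequent on nafithromycin. That is to be expected if nafithromycin is truly inferior, but it is not known.
- **Size is unknown.** No rescue rate is given. The window is short, and a switched subject must be better than baseline in two symptoms, with none worse, by Day 4. Assuming 6% versus 2% or more looks only at the upper part of the plausible range.
- **Part of the problem is already covered.** Switched subjects with no Day 4 assessment count as non-favourable. The CE analysis gives a Day 4 estimate largely free of rescue credit. The MITT analyses at EOT and TOC count rescue as failure. Antibiotic use and significant deviations are tabulated by arm, so an imbalance would be visible.
- **It may be a choice.** Scoring symptoms regardless of other therapy is a treatment-policy approach, and EOT and TOC are investigator-determined cure outcomes of a different kind. The contrast is not an outright contradiction. The protocol, which was not at hand, may also contain a rule.

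These points stand, and they lower the severity. They do not fill the gap. The CE set removes rescued subjects, who are likely failures, instead of counting them. The EOT and TOC analyses address another endpoint, and tabulating antibiotic use does not show how the Day 4 interval would change. If treatment-policy scoring is intended, Section 18.1 does not say so.

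**Conclusion.** The gap is real: the SAP has no Day 4 rule for non-study antibacterials given for CABP, and none of its Day 4 analyses scores such rescue as failure. That it tilts the result toward non-inferiority holds only if rescue with improvement is more frequent on nafithromycin. The shift is zero with equal absolute rescue and reverses with more rescue on moxifloxacin.

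Under the assumed rates the hidden difference is 0.6 to 2.4 points of the 12.5-point margin. At the null boundary, with 5% to 10% of failures in each arm rescued, improved and credited, the false-claim rate would be 3.5% to 4.9% instead of 2.5%. These figures are illustrations and not estimates for this trial. The point is a should-fix: its size may be small, but it touches the only confirmatory test and nothing planned would reveal its effect on that test.

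**What to change.** Before unblinding, add to Section 19.2 a third sensitivity analysis of Day 4 response in the MITT set, using the same Miettinen-Nurminen interval and margin as the primary analysis. In it, any subject who received non-study systemic antibacterial therapy for treatment of CABP, after the first dose and at or before the Day 4 assessment, is scored Unfavourable whatever the symptom change. State in Section 18.1 how such subjects are scored in the primary analysis. Make the composite scoring primary only if that is consistent with the protocol. This is a rule for scoring outcomes and changes nothing in how subjects are treated.

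**Cost.** One extra derivation and one table. Concomitant systemic antibiotics are already summarised (Section 16). The flag also needs the indication and the timing relative to the Day 4 assessment, and Section 16 mentions only drug coding, so their availability in the eCRF should be confirmed. As a sensitivity analysis it does not affect the power of the primary test. If adopted as primary, it would cost about 1 to 3 points of power for an assumed 1 to 3 point fall in both arms.
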